### Interim analyses

Two interim analyses will be performed during the course of the study to determine whether the primary objective of the study has been achieved. The first interim analysis will be performed during enrollment to determine whether it is appropriate to continue enrollment, and the second interim analysis will be performed early after the end of enrollment to determine whether to continue follow-up for the planned period. In either case, if it is determined that the primary objective of the study has been achieved, the study will be terminated, and the results will be promptly published in conferences and papers.

The first interim analysis will be conducted using data from periodic monitoring when half of the expected number of enrolled patients have completed 1 year of follow-up. The second interim analysis will be conducted in conjunction with periodic monitoring at a time deemed appropriate after consultation between the data center and the CRC, around the time when enrollment is completed, and protocol treatment is completed for all enrolled patients. In principle, enrollment will not be stopped during the first interim analysis. The decision criteria based on the results of the interim analysis of this study will be as follows. If the non-inferiority of the mH-P group to the NI group for the primary endpoint is not demonstrated, or if non-inferiority is demonstrated but superiority is not demonstrated, the study will be continued in either case. If non-inferiority of the primary endpoint of mH-P over NI is demonstrated and superiority is also demonstrated, the study will be terminated (effective termination). If the primary endpoint of the mH-P group is lower than that of the NI group, the need for discontinuation of the study will be comprehensively considered without being restricted by statistical judgment such as tests (invalid discontinuation).

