#### Criteria for discontinuing or modifying allocated interventions

If non-inferiority of the mH-P group to the NI group for the primary endpoint is demonstrated, and even if superiority is demonstrated in the interim, the study will be stopped (active discontinuation). In such a case, the need for discontinuation of the trial will be comprehensively considered without being restricted by the statistical judgment of the trial or other factors. If the trial is discontinued, the results will be reported. The enrolled patients will be followed up for 1 year.

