### Oversight and monitoring

An independent data and safety monitoring committee will evaluate the progress of the trial and examine safety variables. The committee will consist of a surgeon, CRCs, and a statistician. Individualized patient description charts including safety parameters will be presented to the committee, including one table comprising these endpoints in blinded groups every 6 months. The main safety parameters are all serious adverse events (AE): mortality, multiple organ failure, anastomotic leakage, pulmonary complications, cardiovascular complications, reinterventions, and reoperation. After the investigators have presented the data, the members of the committee will discuss these results in the absence of the investigators and will then advise them. Possible options will include continuing the trial, performing an interim analysis, adjusting the trial’s design, and discontinuing the trial. Discontinuation will be advised if the committee concludes that the results would convince a broad range of clinicians that one trial arm is inferior or if safety is compromised in one arm. If the committee advises adjustment of the trial’s design, performance of an interim analysis, or discontinuation of the trial, the responsible medical ethical committee will also be notified. Serious adverse events (SAE) will be reported to the chairman of the hospital. The PYNI-GAREREO trial will be monitored according to the Japanese ethical guidelines for medical and health research involving human subjects. This is a low-risk study because both interventions being investigated are considered to be standard care in Japan.

In-house monitoring will be performed every year by a third party to evaluate and improve the progress and quality of the study. A Patient and Public Involvement (PPI) member will not be part of the committee.

The first interim analysis will be conducted after half of the planned number of patients are enrolled, and the second interim analysis will be conducted immediately before the planned patient accrual is completed. The data and safety monitoring committee will review the interim analysis reports independently from the investigators and statistician. In-house monitoring will be performed every 6 months by a data center to evaluate and improve the study progress, data integrity, and patient safety.

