## Trial status

The trial has been recruiting since September 2021. This trial recruitment will end when the planned number of patients have been enrolled or depending on the results of the interim analyses. We plan to conduct two interim analyses. The first interim analysis will be conducted after half of the planned number of patients have been enrolled, and the second interim analysis will be performed immediately before the planned patient accrual has been completed. The data and safety monitoring center will review the interim analysis reports independently from the group investigators and group statistician. If the superiority of the mH-P group is demonstrated with an adjusted α level, the study will be terminated. In-house monitoring will be performed every 6 months by the data center to evaluate and improve the study progress, data integrity, and patient safety.

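### The article gives two incompatible schedules for both interim analyses, neither defined by six-month weights, and contradicts itself on follow-up after stopping

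*Protocol article*

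**What the plan says.** **First look.** Interim analyses sets its purpose: "The first interim analysis will be performed during enrollment to determine whether it is appropriate to continue enrollment". The same section sets its trigger: "when half of the expected number of enrolled patients have completed 1 year of follow-up". Oversight and monitoring has a different trigger: "The first interim analysis will be conducted after half of the planned number of patients are enrolled". Trial status agrees with Oversight and monitoring: "The first interim analysis will be conducted after half of the planned number of patients have been enrolled".

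**Second look.** Interim analyses says "the second interim analysis will be performed early after the end of enrollment to determine whether to continue follow-up for the planned period". It puts the date "at a time deemed appropriate after consultation between the data center and the CRC", within a window around completion of enrolment and of protocol treatment in all patients. Trial status says "the second interim analysis will be performed immediately before the planned patient accrual has been completed", and Oversight and monitoring says the same in nearly the same words.

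**After stopping.** The section on discontinuing or modifying allocated interventions says, for a trial that is discontinued, "The enrolled patients will be followed up for 1 year".

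**Stopping level.** Trial status says that the trial ends if superiority is shown at an adjusted alpha level. The article gives no value for it.

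**The concern.** The two triggers for the first look are about 13 months apart if surgery follows enrolment by a month (Table 1 puts enrolment at 28 days before surgery). The primary endpoint is read at six months. One trigger counts patients who may not yet have been operated on, and the other counts patients six months past the endpoint. The number of six-month weights at either look is therefore a by-product of accrual speed.

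An adjusted alpha level depends on how much primary-endpoint data each look contains. If the sections disagree on when the looks occur, the same interim result could end the trial under one section and not under another.

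The second look has a further problem. One section gives it the task of deciding whether follow-up goes on, while another keeps enrolled patients under follow-up for a year after discontinuation. If the boundary were crossed, staff could not act on both.

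**Working it through.** **No plan figure to reproduce.** The article states no accrual period, no amount of information per look and no adjusted alpha value. The calculation shows how far the two schedules diverge.

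**Inputs from the article.** Total 140 (Abstract, Sample size); two-sided alpha 0.05 (Sample size); endpoint at 6 months and follow-up to 12 months after surgery (Outcomes, Follow-up).

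**Assumptions.** Uniform accrual over A = 24 to 60 months; surgery 1 month after enrolment; no loss to follow-up. A common loss rate would lower all counts in proportion and leave the information fractions unchanged.

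**Formulas.** At month t, six-month weights = 140 × (t − 7)/A.
- Half enrolled: t = A/2, giving 70 − 980/A weights.
- Half with 1 year: t = A/2 + 13, giving 70 + 840/A weights, with 70 + 1820/A enrolled (at most 140).
- First-look nominal p, Lan-DeMets O'Brien-Fleming-type spending at two-sided 0.05: 2 × [1 − Φ(1.96/√f)], where f = weights/140.

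| A (months) | Weights, half enrolled (f) | p | Weights, half with 1 year (f) | p | Enrolled at the 1-year trigger |
|---|---|---|---|---|---|
| 24 | 29 (0.21) | 0.00002 | 105 (0.75) | 0.024 | 140 |
| 36 | 43 (0.31) | 0.0004 | 93 (0.66) | 0.016 | 121 |
| 48 | 50 (0.36) | 0.0010 | 88 (0.63) | 0.013 | 108 |
| 60 | 54 (0.39) | 0.0016 | 84 (0.60) | 0.011 | 100 |

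The number of weights differs by a factor of 1.6 (84/54) to 3.6 (105/29). The threshold differs about seven-fold at 60 months (0.0114/0.0016) and more with faster accrual. As a slower case, take 20 patients a year with no surgical lag: 60 versus 80 weights (f = 0.43 versus 0.57) and p of about 0.003 versus 0.009, still three-fold.

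**Is the 1-year trigger during enrolment?** Only if A/2 + 13 < A, that is, A > 26 months. With accrual of about 26 months or less, the section's trigger falls after enrolment has ended and defeats its own stated purpose.

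**Second look, Interim analyses schedule (all operated, t = A + 1).** All 140 are enrolled, so none can be spared. Six-month weights = 140 − 840/A = 105 to 126, so 14 to 35 patients would lack the primary endpoint if follow-up stopped there.

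**Second look, the other schedule (taken as 139 enrolled).** One patient, or at most the last few, is not yet enrolled. A further 140/A, about 2 to 6, are enrolled but not yet operated on.

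**Cost of the second look.** Take looks at information 0.5 and 1, then add one at 0.9. The final nominal level falls from 0.048 to 0.037, or from 0.049 to 0.040 if the spending function is applied at 0.025 per side. With an effect set for 80% power in a fixed design, power falls from 79.7% to 78.6%, or from 79.9% to 79.0%. That is about one percentage point.

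**The case against.** The best defence is that the statistical analysis plan or full protocol, neither of which is shown, may define the adjusted level, and that a spending function sets boundaries from the information actually observed and needs no fixed look times. This stands in part: one cannot say that the boundary is undefined. It does not remove the contradiction. A spending function adapts to whatever date is used, but the three sections still disagree on the date, and the threshold at the first look moves with it.

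Some stronger readings are tempting and are not supported:

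- **The second look can spare nobody.** This holds only on the Interim analyses schedule. On the other schedule the last one or few patients remain.
- **Stopping would cut the 9- and 12-month outcomes.** The discontinuation section keeps 1-year follow-up. What is established is a conflict between two sections; loss of data is not certain.
- **The second date is a free choice that accumulating data could steer.** It has a stated window, and nothing in the article indicates timing driven by results.
- **No version has any link to the endpoint.** Patients with 1 year of follow-up have passed six months. The flaw is that the number with the endpoint is not fixed.
- **The second look serves no purpose and must go.** Interim analyses gives a purpose, prompt publication, and its criteria also allow discontinuation to be considered if the pyloroplasty arm does worse. The power cost is small. Removing the look is a design preference.

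**Conclusion.** The point holds as a contradiction in current text. Three sections give two schedules for both looks, and two sections disagree on follow-up after stopping. This needs no assumption.

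The size does rest on assumptions. With 24 to 60 months of accrual and a one-month lag to surgery, the first look has 29 to 54 or 84 to 105 six-month weights, and an O'Brien-Fleming-type threshold differs at least seven-fold (about three-fold in the slower case shown). Counts shift with accrual, and other boundary types would give other ratios. The gap of about 13 months between the two triggers rests only on the lag to surgery.

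It should be corrected before either interim analysis is run. That the second look offers little is a secondary observation: it can spare few or no patients and costs about one point of power.

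**What to change.** 1. State one rule, in identical terms, in Interim analyses, Oversight and monitoring, and Trial status. Define each efficacy look by a fixed number of patients with a six-month weight, for example the first when 70 have it. Under the same assumptions that falls at month A/2 + 7, which is during enrolment whenever accrual takes more than 14 months.
2. Replace the discretionary date of the second look with such a count.
3. Reconcile Interim analyses with the discontinuation section: stopping for efficacy ends randomisation only, and every randomised patient completes the planned 12-month data collection.
4. Consider whether the second look is still useful. Keeping it with a defined count is acceptable; dropping it is optional.

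The cost is protocol wording. A first look at 70 six-month weights comes about 7 months after half are enrolled and about 6 months before half have 1 year of follow-up, so against the half-enrolled schedule the early readout is later. If the second look is dropped, the readout shortly before the final analysis is lost.

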### Oversight and monitoring

An independent data and safety monitoring committee will evaluate the progress of the trial and examine safety variables. The committee will consist of a surgeon, CRCs, and a statistician. Individualized patient description charts including safety parameters will be presented to the committee, including one table comprising these endpoints in blinded groups every 6 months. The main safety parameters are all serious adverse events (AE): mortality, multiple organ failure, anastomotic leakage, pulmonary complications, cardiovascular complications, reinterventions, and reoperation. After the investigators have presented the data, the members of the committee will discuss these results in the absence of the investigators and will then advise them. Possible options will include continuing the trial, performing an interim analysis, adjusting the trial’s design, and discontinuing the trial. Discontinuation will be advised if the committee concludes that the results would convince a broad range of clinicians that one trial arm is inferior or if safety is compromised in one arm. If the committee advises adjustment of the trial’s design, performance of an interim analysis, or discontinuation of the trial, the responsible medical ethical committee will also be notified. Serious adverse events (SAE) will be reported to the chairman of the hospital. The PYNI-GAREREO trial will be monitored according to the Japanese ethical guidelines for medical and health research involving human subjects. This is a low-risk study because both interventions being investigated are considered to be standard care in Japan.

In-house monitoring will be performed every year by a third party to evaluate and improve the progress and quality of the study. A Patient and Public Involvement (PPI) member will not be part of the committee.

The first interim analysis will be conducted after half of the planned number of patients are enrolled, and the second interim analysis will be conducted immediately before the planned patient accrual is completed. The data and safety monitoring committee will review the interim analysis reports independently from the investigators and statistician. In-house monitoring will be performed every 6 months by a data center to evaluate and improve the study progress, data integrity, and patient safety.

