### Eligibility criteria

#### Population

All male or female patients with resectable esophageal carcinoma or esophagogastric junction cancer will be screened for eligibility by two esophageal surgeons. The patients will undergo MIE and gastric remnant reconstruction for radical treatment of esophageal cancer or esophagogastric cancer. Two expert esophageal surgeons ([name]) will perform or assist all interventions.

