#### Randomization

After confirmation of the eligibility criteria, registration will be completed by a web-based system to the UMIN Clinical Trials Registry system. The CRCs will enter the registration details into the system. The minimization method will be used for randomization. The staff member who will assess the blinded medical reports will also be blinded. Patients will be randomized to the intervention group or control group in a 1:1 ratio using a computerized randomization tool (UMIN INDICE cloud) with the minimization method, balancing the arms according to age, clinical TNM stage, and change in preoperative body weight during the most recent 6 months before surgery. The two arms will be the mH-P arm (intervention) and the NI arm (control). Because this trial will involve different surgical techniques, complete blinding of the treating surgeons and medical staff is not feasible. The surgeon will know which operation has been performed, and the medical staff can determine whether the patients have undergone pyloroplasty or not by reading the official medical records. However, a study team member will assess blinded medical reports regarding mH-P or NI to ensure a blinded assessment of the primary outcome parameter.

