Do you break out in a cold sweat within about 30 min after eating?	□	□	□	□	□
Do you experience palpitations within approximately 30 min after eating?	□	□	□	□	□
Do you experience dizziness within approximately 30 min after eating?	□	□	□	□	□
Does your stomach rumble within about 30 min after eating?	□	□	□	□	□
Do you have abdominal pain within about 30 min after eating?	□	□	□	□	□
Does your whole body become sluggish and weak 2 to 3 h after eating?	□	□	□	□	□
Do you feel sleepy 2 to 3 h after eating?	□	□	□	□	□
Do you break out in a cold sweat 2 to 3 h after eating?	□	□	□	□	□
Do you have diarrhea?	□	□	□	□	□

The short-term outcomes evaluated in this study will be postoperative complications and the length of hospital stay. Postoperative complications in this trial are defined as anastomotic leakage, stricture, pneumonia, recurrent nerve palsy, surgical site infection, and chylothorax.

The routinely placed jejunostomy enteral tube will be removed within 3 months postoperatively in the outpatient clinic when the patient has been determined to have no risk of reduced oral intake. If the tube feeding is used for a longer period, the prolonged time will be one of the outcome parameters.

Long-term recurrence and the prognosis will also be followed up.

Patients will be blinded to which group they are in, but the physician who performs the surgery and performs the imaging and follow-up will not be blinded to whether pyloroplasty is performed. The dietitian, nurse, and data analyst who evaluate the nutritional status and gastrointestinal symptoms will be blinded to which group each patient is in.

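### The investigators, who may include the unblinded surgeons, present the six-monthly safety table by coded group; it should go from the data center to the committee's closed session, with the key available

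*Protocol article*

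**What the plan says.** All references are to the Protocol article.

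- **What the committee is shown.** Oversight and monitoring: "Individualized patient description charts including safety parameters will be presented to the committee". The same sentence adds a summary by coded group, worded as "including one table comprising these endpoints in blinded groups every 6 months". The endpoints are serious adverse events, among them death, leakage, pulmonary and cardiovascular events, reintervention and reoperation.
- **Who presents it.** Same section: "After the investigators have presented the data, the members of the committee will discuss these results in the absence of the investigators". The committee then advises the investigators.
- **What the committee must judge.** Same section: it advises discontinuation if it concludes that "the results would convince a broad range of clinicians that one trial arm is inferior or if safety is compromised in one arm".
- **Who knows the allocation.** Randomization: "The surgeon will know which operation has been performed". Outcomes: "the physician who performs the surgery and performs the imaging and follow-up will not be blinded to whether pyloroplasty is performed". Population says that two expert surgeons "will perform or assist all interventions", and Study setting gives a single hospital.
- **Formal interim analyses.** These have their own rule in Oversight and monitoring, repeated in substance under Trial status: "The data and safety monitoring committee will review the interim analysis reports independently from the investigators and statistician".

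**The concern.** Coding the groups in a safety table protects against readers who do not know individual allocations. Here the presenters are the investigators, and at a single center with two operating surgeons that group may well include people who know the allocation of every patient. For such a presenter the code may hide little. For the committee, the code stands between the data and the judgment it has to make.

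Two things are at stake.

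1. **Exposure of the investigators.** Surgeons screen patients (Population), operators obtain consent (Informed consent), and the unblinded physician does the follow-up (Outcomes). Removal of the feeding tube rests on a judgment about oral intake (Outcomes). A regular, complete tally by group could color how patients in each arm are managed, and management bears on weight at 6 months. An effect on who is offered the trial is also conceivable. Because allocation comes after enrollment through a computerized minimization tool, that would mainly affect generalizability rather than the contrast between arms.
2. **Direction of a safety signal.** An excess in one coded group calls for different advice depending on whether that group had pyloroplasty or not.

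**Working it through.** No figure in the plan is involved, so the check sets the stated procedures side by side.

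**Step 1: is the table part of what the investigators present?** The article says that charts and table are presented to the committee and, a few sentences later, that the investigators present the data before withdrawing. No other presenter is named for the six-monthly review. The natural reading is that the table is included.

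**Step 2: what can a presenter who knows allocations read from coded columns?** Suppose one row has *a* events in group A and *b* in group B.

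- If *a* = *b*, the row reveals nothing about the key.
- If *a* ≠ *b*, a presenter who knows the arms of the *a* + *b* patients concerned knows which column is which.
- In the simplest case, one event against none, knowing the arm of one patient is enough.
- There is only one key for the whole table, so solving one row makes every row readable by arm.

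The patient charts shown with the table make the matching easier.

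**Step 3: what can the committee read from the same columns?** It can see that one group is worse. The table alone does not say which. Whether the charts disclose the procedure is not stated, so it cannot be said that the committee sees nothing but masked data.

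**Step 4: compare with the formal interim reports.**

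| | Six-monthly safety review | Formal interim analyses |
|---|---|---|
| Content | Serious adverse events | Primary objective (weight loss) |
| Route | Presented by the investigators | Reviewed independently of investigators and statistician |
| Can lead to stopping | Yes | Yes |

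The two streams carry different data, so both rules can hold together. What differs is the protection: both can end the trial, but only one is shielded from the investigators.

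**Step 5: who could take over the table?** Oversight and monitoring and Trial status both describe in-house monitoring every 6 months by a data center, so a suitable body already works to the same calendar.

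**The case against.** The strongest reply is that the table adds little to what the surgeons already know. They take part in every operation, know each allocation, and follow the patients in one hospital. They can count deaths, leaks and reoperations by arm without any report. That exposure comes from an open surgical trial at one center, and a pooled table would not remove it. This largely stands and limits the gain. What the presentation adds is a complete tally by group, assembled for them every six months.

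Four stronger readings are tempting, and the documents do not support them.

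- **That the section contradicts itself.** A reader might set the investigators' presentation against the rule on independent review. That rule covers the formal interim analysis reports, not the six-monthly safety material.
- **That investigators see interim efficacy results.** The listed endpoints are serious adverse events, and weight is not among them. The stated route for primary-endpoint reports excludes the investigators.
- **That the presenters are the operating surgeons.** The article says only that they are investigators. Overlap is a fair inference at one center, but it remains an inference.
- **That the code would break at an early review.** The mortality range of 1.6% to 2.8% quoted in the Discussion gives 140 × 0.016 = 2.24 to 140 × 0.028 = 3.92 deaths over the whole trial, if the national rates apply. Without an accrual rate this says nothing about timing.

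On the committee's side, a route for breaking the code may sit in a charter or the full protocol. Its absence from an article is not a fault.

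**Conclusion.** The point holds in a limited form. The article fixes a procedure in which the investigators present safety data split by coded group, and at this center the coding may not keep the comparison from them. The same coding is applied to the committee, which must reach a conclusion about one arm.

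The size is modest and cannot be put as a number. Sample size, significance level, power and the analysis of weight loss are untouched. The change would reduce investigator exposure somewhat, without removing what surgeons know from care, and would let the committee read the direction of a safety signal from the table itself.

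The conclusion rests on two assumptions: that the table is among the data the investigators present, which is the natural reading, and that the presenters include people who know allocations, which is plausible but unstated. If neither surgeon presents or attends, the exposure limb weakens and the matter of the committee's key remains.

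**What to change.** In Oversight and monitoring:

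1. Have the investigators present only pooled accrual, compliance and safety data, both arms combined.
2. Have the data center send the by-group safety table directly to the committee for its closed session, with the group key available to the committee.
3. State that investigators receive no by-group summaries before the final analysis or a stopping recommendation.

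The cost is small: a change of wording and the redirection of one table to a body that already monitors every six months. No endpoint, sample size or treatment is affected. The drawback is that the investigators see less interim information.
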